## 8. Adverse events, adverse device effects and device deficiencies

### 8.1. Definitions

#### 8.1.1. Adverse Event

An Adverse Event (AE) is untoward medical occurrence, unintended disease or injury or any untoward clinical signs, including an abnormal laboratory finding, in subjects, users or other persons, in the context of a clinical investigation, whether or not related to the investigational device.

This definition includes events that are anticipated as well as unanticipated events.

This definition includes events occurring in the context of a clinical investigation related to the investigational device, the comparator or the procedures involved.

#### 8.1.2. Adverse Device Effect

An Adverse Device Effect (ADE) is any AE related to the use of an investigational medical device.

This definition includes adverse events resulting from insufficient or inadequate instructions for use, deployment, installation, or operation, or any malfunction of the investigational medical device.

This definition includes any event resulting from use error or from intentional misuse of the investigational medical device.

In the context of the current study the rehabilitation tool is considered equivalent with "Device" above.

#### 8.1.3. Serious Adverse Event

A Serious Adverse Event (SAE) is any AE that led to any of the following:

- a) death,
- b) serious deterioration in the health of the subject, that resulted in any of the following:
  - i. life-threatening illness or injury,
  - ii. permanent impairment of a body structure or a body function,
  - iii. hospitalization or prolongation of patient hospitalization,
  - iv. medical or surgical intervention to prevent life-threatening illness or injury or permanent impairment to a body structure or a body function,
  - v. chronic disease,
- c) fetal distress, fetal death or a congenital physical or mental impairment or birth defect

#### 8.1.4. Serious Adverse Device Effect

A Serious Adverse Device Effect (SADE) is an ADE that has resulted in any of the consequences characteristic of a serious adverse event.

SAEs related to procedures imposed by the clinical investigation plan but not with the use of the device should not be considered Serious Adverse Device Effects.

In the context of the current study the rehabilitation tool is considered equivalent with "Device" above.

#### 8.1.5. Unanticipated Serious Adverse Device Effect

An Unanticipated SADE is an effect which by its nature, incidence, severity or outcome has not been identified in the current risk assessment. Procedures associated with the use of a device should be addressed in the risk assessment, which makes it possible to determine whether the procedure related SAEs are Unanticipated Serious Adverse Device Effect or not.

SAEs related to procedures imposed by the clinical investigation plan but not with the use of the device should not be considered Serious Adverse Device Effects.

For the anticipated adverse device effects, see section 4.2 above.

In the context of the current study the rehabilitation tool is considered equivalent with "Device" above.

#### 8.1.6. Device Deficiency

A Device Deficiency (DD) is any inadequacy in the identity, quality, durability, reliability, safety or performance of an investigational device, including malfunction, use errors or inadequacy in information supplied by the manufacturer.

In the context of the current study the rehabilitation tool is considered equivalent with "Device" above.

## 8.2. Recording and Reporting

### 8.2.1. Recording

The PI or an authorized designee will record in the eCRF:

- all AEs except the events below specified not to be recorded:
  - Vertigo, nausea or mild discomfort during the vestibular rehabilitation, regardless of randomization allocation. These symptoms are common after acute vertigo and during vestibular rehabilitation and all subjects are expected to develop such symptoms.
  - Falls and fractures are recorded and reported as stand-alone endpoints and therefore not included in the AE reporting.
  - VSS-SF (Vertigo Symptom Scale - Short Form) measures the frequency of 15 known vestibular symptoms and these are recorded and reported as endpoints and therefore not included in the AE reporting.
- all SAEs
- all DDs
- any new finding in relation to any of the above-mentioned events.

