### 4.2. Anticipated adverse device effects

Mild discomfort may arise from performing the prescribed exercises (see 4.3). Since these exercises are the same ones as those prescribed during standard care (although with higher expected compliance) no additional ADEs are expected apart from those arising from standard care.

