### 4.3. Risks associated with participation in the clinical investigation

Online vestibular rehabilitation involves head movements corresponding to shaking the head (head movement signaling "no") and head movements corresponding to nodding ("yes") under different gaze conditions (open eyes accompanying the movement, closed eyes, open eyes that fixate objects) and different body positions (sitting, standing, walking). These exercises are harmless and well tried for a long time. The same movements are recommended in the written standard instructions that are used at many centers and that also will be used in the study. Discomfort in the form of nausea and dizziness occurs during vestibular rehabilitation (and is a prerequisite for recovery), but we assess that the study

does not involve an increased discomfort compared with standard treatment for the subjects. The main risk associated with malfunction of the online vestibular rehabilitation tool is inadequate rehabilitation.

Subjects will be expected to invest time on study participation and are asked to answer questions about their health, which can be perceived as violating privacy.

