## 6.3. Measurement of variables

The VSS-SF measures the frequency of 15 vestibular symptoms on a scale from 0 (no symptoms) to 4 (symptoms most days) during the past month. The score range is 0–60 and a difference from baseline of  $\geq 3$  points indicate a clinically significant change. The time frame (1 month) for the symptoms will be left as is for the evaluations at week 6 and after 3 months but for the baseline measurement the participants will be asked to report their symptoms during the last 24 hours; and the two response alternatives indicating the highest frequencies (3, quite often [every week] and 4, very often [almost every day]) will be modified to: 3, quite often (almost every hour) and 4, very often (almost all the time). Although this is a deviation from the original version of the VSS-SF this modification is necessary to capture the short-term status of participants soon after vertigo onset. The modified VSS-SF data will be used for the baseline symptom intensity assessments only.

The DHI (range 0–100 points, 0–30 mild, 31–60 moderate and  $\geq 61$  severe dizziness) investigates the effects of dizziness on everyday living. The between group mean DHI score will be compared at each time point as detailed in the statistics section. The scale has subcategories (physical, emotional and functional for DHI) and these will be analyzed separately as exploratory analyses although the total scores will be used for the secondary outcomes.

EQ-5D is an generic instrument which consists of five sub-domains (mobility, self-care, usual activities, pain/discomfort and anxiety/depression) with three severity levels (no, moderate and severe problems). For the current study, the Swedish version EQ-5D-3L will be applied, and the Swedish value set based on experienced health states will be applied to

obtain a health utility score in order to calculate quality-adjusted life years (QALYs). The UK MvH value set will be applied for sensitivity analyses.

The T25-FW data will be collected by using the mean (seconds) of two, timed attempts at walking a clearly marked 25-foot course.

Basic body sway data will be collected by using a locally developed application which utilizes cell phone built-in motion tracking. An enhanced gait analysis with a wearable motion tracking system will be performed at Umeå University Hospital for in-depth measurements.

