### 8.3. List of foreseeable Adverse events

Vertigo, nausea or mild discomfort during the vestibular rehabilitation, regardless of randomization allocation. These symptoms are common after acute vertigo and during vestibular rehabilitation and all subjects are expected to develop such symptoms. Weekly evaluations of these symptoms are included in the online tool and the training intensity is automatically tailored based on symptom intensity. For those randomized to standard care, instructions on lowering training intensity in case of severe discomfort will be given together with the training instructions. The test circumstances at the sites will be designed to provide a safe environment ensuring that no participant will lose balance and fall during walking test.

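### Section 8.2.1 exempts non-serious vertigo and nausea during training from adverse event recording without a severity limit, and no measure stated for both arms shows whether training provoked severe symptoms or was stopped because of them

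*Protocol*

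**What the plan says.** Section 8.2.1 asks sites to record "all AEs except the events below specified not to be recorded". Three exemptions follow, two of which matter here.

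- **Training symptoms.** The exempt events are "Vertigo, nausea or mild discomfort during the vestibular rehabilitation, regardless of randomization allocation". The reason given is that such symptoms are common after acute vertigo and during rehabilitation, and are expected in every subject.
- **VSS-SF symptoms.** The scale "measures the frequency of 15 known vestibular symptoms and these are recorded and reported as endpoints and therefore not included in the AE reporting". This bullet is not confined to symptoms during training.

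All serious adverse events and all device deficiencies stay recordable.

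Other sections bear on severity and exposure:

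- Section 4.2 anticipates mild discomfort from the exercises. It adds that they match standard care, "although with higher expected compliance) no additional ADEs are expected apart from those arising from standard care".
- Section 4.3 gives the sponsor's assessment that the study "does not involve an increased discomfort compared with standard treatment for the subjects".
- Section 6.3 says "The VSS-SF measures the frequency of 15 vestibular symptoms", each rated 0 to 4, with the past month as the time frame at week 6 and month 3.
- Section 8.3 says that the tool evaluates symptoms weekly and tailors training to their intensity. For controls, "instructions on lowering training intensity in case of severe discomfort will be given together with the training instructions".
- The only safety endpoint (section 5.2) is falls and fractures.

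**The concern.** The tool prescribes the same movements as the leaflet, and section 4.2 expects participants to do more of them. Symptoms provoked by that extra exposure are the most plausible harm of the device, and the section 8.2.1 exemption falls on them.

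Take a participant whose exercises bring on severe but non-serious vertigo, and who cuts back or stops training. Followed as written, section 8.2.1 gives no adverse event in either arm. Without a recorded event, the causality assessment in section 8.2.3 and the follow-up of device-related events in section 8.4 have nothing to act on.

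The instructions for use in section 2.5 tell participants, without the qualification found in section 4.3, that taking part brings no more discomfort than standard treatment. They ask participants to contact staff about problems beyond that. Section 3.3 describes the trial as pivotal and confirmatory, and section 13 plans general release of the tool if the primary endpoint is positive. A tolerability statement of this kind should have data behind it that can be compared between arms.

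**Working it through.** No sample size, power or error rate is involved, so the check sets the sections side by side.

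**1. How far the first exemption reaches.** Read grammatically, mild limits discomfort only. Vertigo and nausea are then exempt up to the threshold of seriousness, while discomfort above mild stays recordable. But section 4.3 describes the discomfort of rehabilitation as nausea and dizziness. The same episode can therefore be exempt if entered as nausea and recordable if entered as severe discomfort. Sections 4.2 (mild only), 8.2.1 (mild for one of three terms) and 8.3 (severe foreseen) give no common rule, and sites could classify the same event differently.

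**2. Whether the VSS-SF fills the gap.** Fifteen items with a maximum of 4 give 15 × 4 = 60, which matches the stated range of 0 to 60. The whole score is made of frequency ratings; no part of it grades severity or ties a symptom to training. The protocol does not list the 15 items, so the exact reach of the second exemption cannot be read from it.

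**3. What other sources give.**

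| Source | Arms | Severity of training-provoked symptoms | Stopping training because of symptoms |
|---|---|---|---|
| Adverse event form (8.2.1) | Both | Discomfort above mild; vertigo and nausea only if serious | Not for exempt symptoms |
| VSS-SF (6.3, Table 1) | Both | No, frequency only | No |
| DHI (6.3, Table 1) | Both | No, effect of dizziness on everyday life | No |
| EQ-5D-3L (6.3, Table 1) | Both | No, generic health state | No |
| Session counts (Tables 1 and 2) | Both | No | Shows fewer sessions, not why |
| Weekly scores in the tool (6.7, 8.3) | Intervention only | Discomfort scored | Not stated; transfer to the eCRF not stated |
| Termination form (6.6.3) | Both | No | Reason for leaving follow-up; none stated when only training stops |
| Falls and fractures (5.2) | Both | No | No |

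No source is stated that covers either of the last two columns in both arms for vertigo and nausea.

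**4. How much a change could still capture.** Section 9.6 reports 138 included on 25 April 2023, of whom 129 had reached week 6; the target is 184.

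- Not yet at week 6: 184 − 129 = 55, and 55/184 = 29.9%.
- Not yet included: 184 − 138 = 46, and 46/184 = 25.0%.

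At that date, new questions could reach at most 55 participants at week 6. Only the 46 still to be included were certain to have both contacts ahead of them. Any later start lowers these numbers.

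**The case against.** The strongest defence is that the exemption is a reasoned choice. It applies to both arms alike. The exempt symptoms belong to the disease and are also the primary outcome, and early after acute vertigo it is hard to attribute an episode to exercise rather than illness. Recording every episode would swamp the adverse event data. The section 4.3 statement is a risk judgement, not an objective or endpoint. All this stands as an argument for exempting mild, expected symptoms. It does not explain why the exemption has no severity limit for two of its three terms, or why sections 4.2, 8.2.1 and 8.3 differ.

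A reader might infer more than the text supports:

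- **That symptoms of every severity go unrecorded.** Serious events are recorded and, on the literal reading, so is severe discomfort named as such.
- **That the trial has nothing to compare between arms.** Session counts, VSS-SF at week 3, DHI and EQ-5D are collected in both arms and give indirect signals.
- **That the VSS-SF is the stated substitute for recording training symptoms.** That exemption rests on expectedness; the scale justifies a separate bullet.
- **That the report will show hardly any device effects.** Adverse events outside the listed exemptions, and all device deficiencies, remain recordable.
- **That the benefit-risk rationale in section 4.5 depends on equal discomfort.** That section does not mention discomfort.

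The investigator's brochure and risk analysis report are not shown. Either might provide for use of the tool's scores, but those scores have no counterpart in the control arm in the protocol.

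**Conclusion.** The concern holds as a gap in harm capture. Non-serious vertigo and nausea during training are exempt without a severity limit, more widely than section 4.2 anticipates. The VSS-SF exemption relies on a scale that does not grade severity. The section 4.3 assessment therefore cannot be checked directly between arms; the available signals are indirect or one-sided.

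The exempt symptoms are expected in all subjects, 184 as planned. The number with severe or training-limiting symptoms is not given and cannot be derived from the protocol, so no rate is offered. The primary endpoint and its analysis are not affected. The conclusion assumes that sites follow section 8.2.1 literally and that no document outside the protocol adds a symptom record for both arms. The change is worth making, mainly because it is cheap.

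**What to change.** - Reconcile sections 4.2, 8.2.1 and 8.3 on the severity of expected symptoms.
- Limit the recording exemption in section 8.2.1 to mild, expected symptoms, and apply the same limit to the VSS-SF bullet.
- At the existing week-3 and week-6 contacts, record in both arms any vertigo, nausea or discomfort during training that was severe or led the participant to reduce or stop training.
- Report the proportion per arm descriptively beside falls and fractures, stating that the data are self-reported and that capture is partial for participants already past week 6.

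This changes recording only. It costs an amendment to one list and a short question at two contacts that already take place. The downsides are more non-serious adverse event entries for sites and incomplete capture: at the section 9.6 count, at most 55 of 184 participants had week 6 still ahead.
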